### Randomization and blinding

Randomization will be performed independently by Fonterra Co-Operative Ltd, using Microsoft Excel and a computer-generated random number list according to procedures explained by Kim and Shin [35]. Randomization will be performed in blocks of eight and not stratified; however, covariates will be collected and an important selection of these will be used in a sensitivity analysis.

The study is double-blinded for study capsules and only the study statistician will be unblinded after data analysis of the 6-month primary outcome. Outcome assessors and all participants will remain blinded to capsule allocation until all 9-month follow-up data are collected. Due to the obvious difference in cereals the study is not blinded for cereals; however, participants will not be informed of the full rationale for cereal choices, the full contents of cereal packages, or which cereal is considered the intervention and which is the control until after all participants have completed the study.

Fonterra Co-Operative Ltd will share the study cereal allocation codes with the study centre, while capsule allocations will remain double-blinded until data are analysed.

Staff will allocate the next study number in consecutive sequence to those eligible at the commencement of the enrolment visit. The type of cereal allocated will only be revealed to the participant at the time the relevant intervention is dispensed after baseline measures are collected.

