### Information and consent

Potential participants will be provided with trial information through study videos available on a study website, written information and consent forms, and detailed discussions with field staff prior to screening and study enrolment. Information and consent forms will cover participation in the F4H study, and a separate information and consent form for the collection of additional biological samples (faecal samples and blood) to be bio-banked for later analysis.

Field research staff will obtain formal written informed consent at the commencement of the enrolment visit. Participants will attend four morning study visits in a fasted state. See Fig. 2 for the study timeline.

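### As written, the study centre receives the cereal codes and numbers participants in sequence, so staff with access to the codes could know the next cereal before enrolment; concealment of the β-glucan factor is not protected

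*Protocol article*

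**What the plan says.** Five statements in Randomization and blinding fix the procedure.

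- **Codes.** The randomizing company "will share the study cereal allocation codes with the study centre". The same sentence sets capsules apart: "while capsule allocations will remain double-blinded until data are analysed".
- **Numbering.** "Staff will allocate the next study number in consecutive sequence to those eligible at the commencement of the enrolment visit".
- **Blocks.** "Randomization will be performed in blocks of eight and not stratified".
- **Blinding.** "Due to the obvious difference in cereals the study is not blinded for cereals".
- **What is held back, and from whom.** "The type of cereal allocated will only be revealed to the participant at the time the relevant intervention is dispensed", which comes after the baseline measures.

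Information and consent puts consent at the same moment as numbering: "Field research staff will obtain formal written informed consent at the commencement of the enrolment visit".

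The article describes no envelope, electronic release step or separate dispenser that would keep the cereal codes from the staff who enrol.

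**The concern.** Blinding and concealment are different protections. The article explains why the cereals cannot be blinded once dispensed. That does not prevent each allocation from being hidden until the person is irrevocably in the trial, and an open-label comparison can still be concealed in this way. Here the delay shields the participant and not the recruiter.

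A recruiter who knows the next cereal has several ways to influence who receives it, all within the written procedures:

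- The exclusion list ends with an investigator-judgement item on likely compliance or safety.
- A person may be enrolled up to 4 months after screening (HbA1c 41–44 mmol/mol) or up to 1 year after (45–49 mmol/mol), so the order of enrolment can be shifted.
- The number is issued before the baseline measures, so staff could know the cereal while taking them.

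Cereal is one of the two randomized factors in the primary ANCOVA, which also includes the interaction. Any comparison of the combined arm with the double-control arm crosses cereals as well. The six-month changes in HbA1c, BMI, blood pressure and cholesterol then feed the economic model. Selection at enrolment would carry through to all of these.

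**Working it through.** The article gives no figure for predictability, so there is none to reproduce. The check has two parts.

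**1. Reading the statements together**

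| Step | Cereal | Capsule |
|---|---|---|
| Codes given to the study centre | Yes | No, kept blinded until analysis |
| Number issued | Consecutively, at the start of the visit | Same |
| Consent taken | Start of the same visit | Same |
| Allocation withheld from participant | Until dispensing, after baseline measures | Until all 9-month data are collected |
| Allocation withheld from enrolling staff | Not stated | Yes |

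No other allocation step is described, so the study number is taken to fix the arm. If the code list is available at the centre in advance, the next unused number gives the next cereal. In that case every upcoming cereal allocation is knowable. This follows from advance access and is not a calculated figure.

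**2. The favourable reading: codes released one at a time**

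Inputs:
- Block size 8 (Randomization and blinding).
- Allocation 1:1:1:1 (Randomized controlled trial design and hypotheses), hence m = 4 active and 4 control cereals per block.
- 152 participants (Sample size), hence 152 / 8 = 19 blocks.
- Assumptions: staff see each cereal dispensed, and know the block size and where each block begins.

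*Allocations that are certain.* Once one cereal is used up within a block, the rest of the block is determined. Each active place falls after all m control places with probability 1/(m + 1), and the reverse holds for each control place. The expected number of certain allocations is therefore

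2m / (m + 1) = 8 / 5 = 1.6 of 8 = 20%.

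Over 19 blocks: 19 × 1.6 = 30.4, about 30 of 152.

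*Correct guesses.* A person who always guesses the cereal with more places left expects

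m + 2^(2m−1) / C(2m, m) − 1/2 = 4 + 128/70 − 0.5 = 5.33 of 8 = 66.6%.

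Over 19 blocks: 19 × 5.33 ≈ 101 of 152, against 76 by chance.

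An exact recursion over a block of four and four gives the same two values (1.6 and 5.33).

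**The case against.** The strongest reply is that the article says only that codes are shared. The centre must learn the cereal at some point in order to hand it over, so the sentence also fits release at dispensing. The article condenses a full protocol (version 2.1), and the name of the code holder and the time of release are details that an article may leave to it. This stands as far as the facts go: a reader might infer that the next cereal *was* known, or that concealment *was* broken, and the document does not support either. It does not remove the point. The article states a procedure in which codes go to the centre, numbers are consecutive, and the only delay protects the participant. Followed as written, that leaves the next cereal open to enrolling staff.

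The figures in the favourable reading are also conditional. Nothing says that field staff were told the block size or boundaries, and the sequence was generated independently of them.

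The possible harm has limits:
- HbA1c is a laboratory measurement. Weight, waist and blood pressure follow defined protocols with calibrated equipment and duplicate readings, so biased baseline measurement is a minor route.
- Eligibility is assessed beforehand by questionnaire and HbA1c, and all participants are analysed whatever their baseline HbA1c.
- Diet is recorded in 3-day diaries, and adjusted analyses cover BMI, exercise and energy intake. It would be wrong to call diet an unmeasured source of bias. Motivation and expected adherence are not among the listed adjustment variables, so adjustment may be incomplete.

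Finally, Trial status gives February 2018 for the start of recruitment and about April 2019 for completion, and the article appeared on 29 July 2019. A change to enrolment procedure may come too late, so a fallback is needed.

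**Conclusion.** The point holds as a weakness in the stated procedure, confined to the cereal (β-glucan) factor. Centre staff with access to the codes could know the next cereal before a person is consented, numbered and measured, and nothing in the article protects against this. Capsule concealment, and with it the HN001 main comparison, is unaffected as described.

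Size: if the full list was available in advance to enrolling staff, all upcoming cereals were knowable. If codes were released singly, about 67% could be guessed (50% by chance) and about 20% would be certain, provided staff knew the block size and boundaries. These figures describe predictability; the document gives no basis for converting them into a bias in HbA1c. Nor does it show that anyone used the codes to select participants. A statement that the cereal codes were held away from enrolling staff until each person was enrolled would settle the main part of the concern.

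**What to change.** **If enrolment is open.** Keep the cereal list away from the study centre. Have the code holder at the randomizing company, or a non-fieldworker, release one participant's cereal code at a time, by a concealed electronic step or a sequentially numbered opaque envelope. Release it only after consent, confirmed eligibility and completed baseline measures are recorded. For remaining participants, replace the fixed block of eight with undisclosed varied block sizes in multiples of four (for example 4, 8 and 12), which keeps the 1:1:1:1 ratio. The article already routes capsule unblinding through a non-fieldworker contacting the code holder, so the channel exists. The cost is a procedural amendment and a few minutes per enrolment visit, with no added participants or measurements.

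**If enrolment has closed.** State in the trial report who held the cereal codes, in what form and from what date. Present baseline characteristics by cereal factor as well as by the four arms. Review discretionary exclusions and the timing of enrolment against the next cereal in sequence. If enrolling staff had access, qualify the β-glucan comparison, and the economic results that rest on it, accordingly. The cost is one paragraph, one table and a check of existing logs.

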### Setting and participants

Study participants will be predominantly urban-dwelling adults, recruited from the community in the greater Wellington region of New Zealand.

Eligible individuals will be English speaking adults aged 18–80 years who are capable of giving informed consent, who have pre-diabetes, defined as per New Zealand criteria as a screening HbA1c 41–49 mmol/mol (5.9–6.6%) [36]. There is potential for a change in HbA1c between screening and enrolment. To minimize the possibility that those with screening HbA1cs in the lower range will have regressed to the normal range by enrolment, the following criteria will apply. Those with screening HbA1c in the range 41–44 mmol/mol will be enrolled within 4 months of the screening test date, and those with HbA1c in the range 45–49 mmol/mol will enrolled within 1 year of the screening test date. For analysis, only the HbA1c at baseline visit and subsequent time points will be included. Regardless of the baseline HbA1c value, all participant data will be included in the analysis.

In addition, participants will be excluded if any of the following apply:Previous bariatric surgery, or pre-existing T1DM or T2DM. Where a previous diagnosis of T2DM is uncertain, this will be defined as ever having had two consecutive HbA1c results ≥ 50 mmol/mol that are at least 3 months apartAbnormal thyroid function (thyroid-stimulating hormone < 0.3 mU/l or ≥ 4.5 mU/l in the last 18 months); those requiring stable doses of thyroxine for treated hypothyroidism will be eligible for the studyCurrent significant renal disease (estimated glomerular filtration rate < 30 ml/min/1.72m^2^)Serious immune dysfunction (for example HIV/AIDS, immune deficiency diseases)Current pregnancy or breastfeeding, or planning to conceive during the studyUnstable body weight (active weight loss/gain > 5 kg in prior 3 months), or weight > 200 kgStructural heart disease (known valve abnormality or replacement, history of endocarditis) or other vascular implant, apart from cardiac stents or intracranial coilsGastrointestinal disorder that alters the digestion and absorption of nutrients (e.g. ulcerative colitis, Crohn’s disease, an ileostomy or colostomy)Medication use; current use of immune suppressant medications, medications that modify blood sugar levels, or anticipated regular use of such medications (e.g. frequent use of oral or injected steroids), long-term use of systemic antibioticsUse fibre/prebiotic/β-glucan/probiotic supplements and is unable or unwilling to cease using these for the study durationAllergy/intolerances; coeliac disease, intolerance to oats, milk, barley or corn or severe allergy to traces of other allergens that may be present in the study interventionsDoes not agree to refrain from donating blood for 3 months prior to each study visitIs participating in, or has recently participated in, another research study involving an intervention which may alter outcomes of interest to this study, or lives with another participant who is already enrolled in the F4H studyDoes not have a general practitioner/primary healthcare provider or does not agree to study communicating clinical results to the general practitioner if neededAny other condition or situation which, in the view of investigators, would affect the compliance or safety of the individual taking part

### Interventions

#### Study capsules

Active study capsules will contain *L. rhamnosus* HN001 (6 × 10^9^ cfu) and 140 mg corn-derived maltodextrin. *L. rhamnosus* powder will be produced as described by Wickens et al. [37]. Placebo capsules will be identical in appearance and contain 150 mg (corn-derived) maltodextrin. Grain Processing Corp., Oregon, USA, manufacture the maltodextrin, and Salkat New Zealand Ltd, Auckland, will supply it to Fonterra Co-operative Group Ltd. Alaron Products Ltd, Nelson, New Zealand, will encapsulate both powders. An external registered laboratory will undertake safety and quality testing to pharmaceutical standards and compliance with the Therapeutic Goods Act. Fonterra Co-Operative Ltd will supply the capsules in sealed opaque bottles containing 105 capsules.

Study capsules will be maintained in cool storage (4 °C) to preserve probiotic viability. Participants will be instructed to store capsules in their home fridge, and to contact the study centre if they are accidentally left at room temperature for more than 2 days, or left in the hot sun for 30 min or more; under these circumstances, replacement capsules will be issued. Participants will be instructed to take one capsule a day and avoid taking the capsule 10 min before or after eating or drinking hot substances.

Throughout the study, Fonterra Co-Operative Ltd will test capsules returned from the field to ensure probiotic viability is maintained at a minimum of 6 × 10^9^ cfu.

#### Study cereals

Cereals were chosen as the delivery method for the β-glucan prebiotic intervention to enable an adequate dose to be administered in the intervention cereal. In addition, cereals can be administered as a food in a range of formats to increase the variety of options for participants.

The active cereal contains 40 g Uncle Toby’s Flemings Rolled Oats (manufactured by Nestle Australia) and 8 g of OatWell® 28XF oatbran (supplied by DSM Nutritional Products Ltd, Switzerland) or 8 g SWEOAT Bran BG28 XF (the same product; supplied by Swedish Oat Fiber AB, Sweden) (www.sweoat.com). Total β-glucan dose is 4 g. Oatwell 28/SWEOAT Bran BG28 XF is a heat-treated extra-fine oatbran containing 28% high-viscosity-solubility and high-molecular-weight (> 2000 kDa) β-glucan.

The control cereal contains 35 g cornflakes (manufactured by Sanitarium Health and Wellbeing, Auckland, New Zealand) and 8 g non-dairy creamer (C35; manufactured by Shantou City Chenghai District Wenhui Food Co. Ltd, China).

Cornflakes and creamer were chosen as the control cereal as they are expected to have minimal prebiotic effect. Having a control cereal and powder enhances the study design by enabling some masking of which cereal contains the active interventions. Active and control ereals are calorie matched. See Additional file 1 for comparison of cereal nutritional values.

HealthPak Ltd, Penrose, Auckland, New Zealand, will pack the study cereals and supply them in single-serve daily portions. To ensure precise dosing, each individual daily serving contains two opaque packs, one containing the course-grained cereal (oats/cornflakes) and a smaller sachet containing the powder (β-glucan or non-dairy creamer) The two sachets which together constitute a daily serving of cereal are enclosed together in a clear outer package.

Study participants take the full contents of one cereal pack daily for 6 months. Cereals will be used as a replacement for some aspect of the participant’s normal diet, may be taken at any time of the day, and may be taken at a different time to the study capsule if desired. Standard instructions include avoiding or minimizing the addition of sugar, honey, or golden or maple syrup to the cereals to no more than a teaspoon. A recipe card containing serving suggestions will be supplied to each participant. These suggestions were designed through consultation with the ethnic groups known to be at higher risk of diabetes in New Zealand. Recipes are designed to encourage compliance with the study cereals by providing a variety of ways to take the cereals (e.g. hot, cold, or as a smoothie), appeal to differing ethnic food preferences, and actively encourage the use of whole foods to flavour the cereals.

#### Concomitant care

To ensure all participants have access to a similar baseline knowledge of pre-diabetes, all participants will be given a standard information pamphlet about pre-diabetes at the enrolment visit. Study participants will be advised to use the study interventions daily (as described above), and apart from this to continue with their current routines. All participants will be given a record of their anthropometric measures at each study visit. Physical activity levels and dietary intake will be measured by the Stanford Leisure-Time Activity Categorical Item questionnaire (L-Cat 2.2) [38] and 3-day diet diary at every study time point. These data will be used in the analysis to control for the effects of changes in activity and diet.

Throughout the study, all participants will continue with their usual healthcare provided by their general practitioner. Any change to care such as commencing medications which may impact on study outcomes will be collected and adjusted for during the analysis.

#### Adverse effects and modification to study interventions

In previous HN001 studies we have found the probiotic to be safe and well tolerated [20, 39].

All components of the cereal interventions are marketed for human consumption and are therefore not a safety risk. While some individuals require gradual increases when introducing a higher level of fibre into their diet, consumption up to 10 g β-glucan daily is generally tolerated [30]. β-glucans undergo fermentation in the colon, and participants may experience flatulence, bloating, or alteration in bowel habits [30]. Any gastrointestinal effects of interventions will be systematically assessed in questionnaires included in the 3-, 6-, and 9-month follow-up visits.

If any participant reports gastrointestinal symptoms which may relate to the study interventions that are causing discomfort, pain, or impacting on the participant’s ability to take the study interventions, and are not severe enough to require medical review, the following procedure will be followed:Discontinue both capsule and cereal interventions until symptoms settle. In instances where participants clearly relate symptoms to the cereal then they stop the cereal only and continue with the capsule.If symptoms resolve, then they recommence capsules only and continue for a few days to check that no symptoms return.If capsules are tolerated, they begin to reintroduce the cereal. Start the cereal reintroduction by mixing powder with cereal and taking half of the total dose only. Then, after a few days and if tolerated well, gradually increase the dose to the full amount.If at any point symptoms return, they reduce the dose to the level that they can tolerate.If required, to improve tolerability the daily cereal dose may be taken in part doses spread over the day.It is very unlikely that participants would not be able to tolerate either of the interventions; however, should this occur the participant will be encouraged to continue in the study with interventions at levels they can tolerate, and to ensure outcome data are collected for an intention-to treat analysis. Compliance with the interventions will be collected (see below).If symptoms do not resolve on discontinuation of study capsule and cereals, then advise participant to see their usual healthcare provider for further advice and investigation; withhold study interventions until a diagnosis is made and the symptoms are resolved. Then consider reintroduction as per 2–5 above.

#### Adherence to study interventions

Multiple strategies will be used to encourage and monitor adherence to the study interventions. Clear verbal and written instructions will be provided at the enrolment and 3-month visit. Discussion will include assessment of lifestyle patterns and how best to remember to take study capsules, and how to integrate cereals into the individuals’ pattern of eating. Practical aids will be offered, including recipe sheets, a blender for making smoothies, and a reusable 1-week medication dispenser to assist with recalling if the daily capsule has been taken. Two weeks after commencing the study all participants will be contacted to assess how they are managing with taking the interventions; further individualized coaching will be provided if required. In addition, similar discussions will occur at any other time a participant indicates this is needed, and routinely to all participants at the 3-month visit to encourage ongoing adherence.

All unused study capsules and cereals will be returned and counted.

### Outcome measures

The primary outcome is HbA1c after 6 months. HbA1c is chosen as it is currently the most commonly used diagnostic test for pre-diabetes and T2DM in New Zealand [40], and therefore has the most direct relevance to clinical practice.

Secondary outcomes include HbA1c after 3 months and 9 months, which is 3 months after the cessation of the interventions to check if there are persistent effects. Other secondary outcomes include fasting glucose, insulin resistance measured by homeostatic model assessment, fasting lipid profiles, mean systolic and diastolic blood pressure, and anthropometric measures (waist size, body weight, and body mass index (BMI)) at 3 and 6 months. Psychological outcomes include symptoms of depression, anxiety, and stress measured on the shortened version of the Depression Anxiety Stress Scale (DASS 21) [41] and health-related quality of life measured by the short-form health survey version 2 for New Zealand/Australia (SF-36) [42] after 6 and 9 months only. See Table 1 for a summary of outcome measures, and Table 2 for a summary of questionnaire variables. Study questionnaires were pre-tested during the study set up.

**Table 1 Tab1:** Summary of outcome measures

Outcomes	Time point	Measurement
Primary outcome		
HbA1c	At 6 months	Measured from whole blood from K_2_EDTA tube on a Cobas c 311, Roche Diagnostics, Auckland, New Zealand
Secondary outcomes		
HbA1c	At 3 and 9 months	Measured from whole blood from K_2_EDTA tube on a Cobas c 311, Roche Diagnostics, Auckland, New Zealand
Fasting plasma glucose	At 3, 6, and 9 months	Measured from plasma from fluoride/oxalate tube on a Cobas c 311, Roche Diagnostics, Auckland, New Zealand
Fasting insulin		Measured from plasma from K_2_EDTA by Human/Canine/Porcine Insulin DuoSet ELISA R&D Systems Inc.
HOMA-IR		Calculated as HOMA = (glucose (mmol/l) x insulin (pmol/l))/22.5 [43]
Fasting lipid profiles		Measured from fasting serum from SST II Advance Tube as total cholesterol, low-density lipoprotein cholesterol, high-density lipoprotein cholesterol, and triglycerides. Measured on a Cobas c 311, Roche Diagnostics, Auckland, New Zealand
Blood pressure	At 3 and 6 months	Measured as mean systolic and mean diastolic blood pressure using standard calibrated electronic sphygmomanometer and protocol*
Weight		Measured in kg using standard calibrated electronic equipment and protocol*
Waist circumference		Measured in cm using standard equipment and protocol*
Body mass index		Calculated as weight (kg)/height (m)^2^
Depression, anxiety, and stress scores	At 6 and 9 months	Measured using DASS 21. The DASS is a set of three self-report scales designed to measure states of depression, anxiety and stress. It has validated psychometric properties, with good test–retest properties in both clinical and community populations, and is robust across a range of demographic variables [44–48]
Physical and emotional well-being		Measured using SF-36. The SF-36 is a self-completed questionnaire, relating to physical and emotional health over the past 4 weeks. It is a well-validated scale, with good psychometric properties, widely used as a health outcome measure [42, 49–51]. Raw data will be uploaded and analysed on the ‘QualityMetric Health Outcomes TM scoring software 5.1. Permission to use granted on 13 December 2017
Other outcomes		
Adverse events	At 3, 6, and 9 months	Hospitalizations
		Gastrointestinal symptoms and bowel function
Compliance	At 3 and 6 months	Calculated based on return of unused cereal and capsules

*See Additional file 2 for equipment and protocols for anthropometric and blood pressure measures

*DASS 21* Shortened version of the Depression Anxiety Stress Scale, *HbA1c* glycated haemoglobin, *HOMA-IR* homeostatic model assessment of insulin resistance, *SF-36* Short-form health survey version 2 for New Zealand/Australia

**Table 2 Tab2:** Summary of questionnaire variables

Questions	Time point collected	Details	Source
Demographics	Baseline	Name, address, date of birth, ethnicity, income, educational qualifications	Questions based on Statistics New Zealand Census questions 2013, available from http://archive.stats.govt.nz/Census/2013-census/info-about-the-census/forms-guidenotes.aspx.
Diabetes and cardiovascular disease risk factors	Baseline	History of first-degree relative with type 2 diabetes mellitus. Personal history of gestational diabetes, or polycystic ovarian disease (females only), hypertension, dyslipidaemia, myocardial infarction, stoke, mental illness, ethnicity, smoking	Questions based on Ministry of Health 2016 New Zealand Health Survey Adult Questionnaire (Year 6) 1 July 2016–30 June 2017 with some specific additions. New Zealand Health survey available from https://www.health.govt.nz/publication/content-guide-2016-17-new-zealand-health-survey
History of mental health disorders	Baseline and at 6 and 9 months if newly diagnosed since previously collected	History of anxiety, depression, or other mental health illness; current treatments used	Questions based on Ministry of Health 2016 New Zealand Health Survey Adult Questionnaire (Year 6) 1 July 2016–30 June 2017 with some specific additions. New Zealand Health survey available from https://www.health.govt.nz/publication/content-guide-2016-17-new-zealand-health-survey
Recent major stressful life events	Baseline and at 6 and 9 months	History of stressful life events occurring in the preceding 12 months at baseline, and since last recorded at subsequent time points	The Life Stress scale is adapted from the Pregnancy Risk Assessment Monitoring System (Centers for Disease Control and Prevention, 2009), and is a 13-item measure included to address the occurrence of recent stressful experiences
Medications	All	Name, dose, frequency, route of all prescribed medications (except topical), and specific over-the-counter medications	Developed by researchers coded according to World Health Organization Anatomical Therapeutic Chemical Classification System with Defined Daily Doses [52]
Supplement use	All	Confined to probiotics, prebiotic/fibre, fish oils, and plant sterols supplements; name, frequency of use, types of probiotics and prebiotics contained in relevant supplements	Developed by researchers
Background use of foods which may impact outcomes	All	Confined to foods containing probiotics (yogurt and other fermented foods), oats/corn, artificial sweeteners, foods enriched with plant sterols; frequency of use in past month (at baseline) or since previous visit (all other time points)	Developed by researchers
Professional lifestyle modification or mental health advice	All	Has participant received professional advice about lifestyle interventions or mental health (in previous 12 months at baseline, and since last collected at other time points)	Created by researchers based on questions from Ministry of Health 2016 New Zealand Health Survey Adult Questionnaire (Year 6) 1 July 2016–30 June 2017 with some specific additions. New Zealand Health survey available from https://www.health.govt.nz/publication/content-guide-2016-17-new-zealand-health-survey
3-day food diary	All	All foods and drinks including quantities and methods of preparation over 3 days	Data entered into Foodworks 9 (Xyris Software Australia Pty Ltd)
Physical activity measure	All	Six-point descriptive categorical scale used to assess levels of activity, and in relation to recommended activity guidelines. Categories broadly match activity intensity based on metabolic equivalents.	Stanford Leisure-Time activity categorical Item (L-Cat 2.2) [38]
Smoking	All	Classification as non-smoker, ex-smoker, or current smoker and intensity of current smoking	Developed by researchers
Alcohol and recreational drug use	Baseline and at 6 and 9 months	Frequency of alcohol use and number standard drinks taken of a typical day. Use of substances for recreational or non-medicinal purposes to get high. Identifies substances used and frequency of use	Questions based on Ministry of Health 2016 New Zealand Health Survey Adult Questionnaire (Year 6) 1 July 2016–30 June 2017 with some specific additions. New Zealand Health survey available from https://www.health.govt.nz/publication/content-guide-2016-17-new-zealand-health-survey
Gastrointestinal symptoms	At 3, 6 and 9 months	Changes in frequency of gastrointestinal symptoms including nausea/vomiting, stomach aches, cramps, or pain, bloating or swollen stomach/abdomen, and bowel motions. Evaluation of impact of any changes in bowel pattern.	Developed by researchers
Hospitalizations	At 3, 6 and 9 months	Hospitalizations since previous visit (excluding elective surgery and outpatient appointments)	Developed by researchers
Use of reduced dose of cereals	At 3 and 6 months	Yes/no question to determine if participant usually takes half or less of the daily dose of corn/oats, and powder sachet	Developed by researchers

